## Abstract

**Background:**

Diabetes and prediabetes are diagnosed differentially by Western and Chinese medicine. While Western medicine uses objective laboratory analysis of biochemical parameters to define the severity of diabetes and prediabetes, Chinese medicine uses a comprehensive approach that integrates observation, inquiry, pulse palpation, and tongue diagnosis. The medical information collected is then categorized into different syndromes. However, traditional methods of pulse and tongue diagnoses used to determine syndrome differentiation are highly subjective and skill dependent.

**Objective:**

This study aims to identify the gap in conventional traditional Chinese medicine (TCM) diagnostic techniques for syndrome differentiation analysis using contemporary diagnostic devices. We devised a protocol for a nonrandomized, exploratory, observational case-control study with equal allocations in 5 arms to investigate the syndrome differentiation of diabetes and prediabetes. We hypothesize that the TCM syndrome differentiation of diabetes and prediabetes in the tropical climate may differ from that defined based on the Chinese demographic. We also speculate that the high-frequency spectral energy may reflect a difference in pulse wave intensity and density between the healthy and diabetes groups.

**Methods:**

A total of 250 eligible participants will be equally assigned to 1 of 5 arms (healthy or subhealthy, prediabetes, diabetes, prediabetes with hypertension and dyslipidemia, and diabetes with hypertension and dyslipidemia). Participants aged 21-75 years, of any sex or race, and have been diagnosed with diabetes (fasting plasma glucose [FPG] of 7 mmol/L, or 2-hour plasma glucose [2hPG] of 11.1 mmol/L) or prediabetes (impaired FPG of 6.1-6.9 mmol/L, or impaired glucose tolerance with an 2hPG of 7.8-11 mmol/L) will be included. The Health Evaluation Questionnaire, Physical Activity Questionnaire, sugar intake assessment, Constitution in Chinese Medicine Questionnaire, radial pulse diagnosis, and tongue diagnosis will be performed in a single visit. ANOVA for continuous data and chi-square tests of independence will be used for categorical data assessments, with a level of *P*<.05 considered significant.

**Results:**

The recruitment is in progress. We anticipate that the study will conclude in June 2025. As of July 15, 2024, we have enrolled 140 individuals.

**Conclusions:**

To the best of our knowledge, this is the first study to use contemporary TCM diagnostic instruments to map expert and empirical knowledge of TCM to its scientific equivalents for the purpose of evaluating the syndrome differentiation of diabetes. We designed this protocol with the exploratory goal to examine objectively the syndrome differentiation of patients with diabetes and those with prediabetes using TCM diagnostic technologies. The data collected and evaluated under standardized conditions using these contemporary diagnostic devices will exhibit a higher degree of stability, hence yielding dependable and unbiased results for syndrome differentiation. Thus, our findings may potentially increase the accuracy of identification, diagnosis, treatment, and prevention of diabetes and prediabetes through a system of targeted treatment.

**Trial Registration:**

ClinicalTrials.gov NCT05563090; https://clinicaltrials.gov/ct2/show/NCT05563090

**International Registered Report Identifier (IRRID):**

DERR1-10.2196/56024

## Introduction

### Definition

Diabetes mellitus is one of the top 10 leading causes of mortality, presenting a significant burden on global public health [1]. The International Diabetes Federation estimates that the global diabetes prevalence among individuals aged 20-79 years will increase from 10.5% (536.6 million) to 12.2% (783.2 million) in 2045 [2]. Prediabetes (intermediate hyperglycemia), characterized by a glycemic level between normal glucose tolerance and diabetes, maintains a high risk of developing diabetes, with an annual conversion rate of 5%-10% [3]. Table 1 provides the World Health Organization (WHO) diagnostic standards defined for diabetes and prediabetes [4]. The American Diabetes Association also states that the glycated hemoglobin A_1c_ (HbA_1c_) level should be at or above 6.5% for diabetes and between 5.7% and 6.4% for prediabetes [5]. The projected global prevalence of patients with impaired fasting glucose and impaired glucose tolerance is 6.5% (414 million) and 10.0% (638 million), respectively [5].

**Table 1 table1:** The WHO^a^ definition of diabetes and prediabetes.

Type and test				WHO criteria		
**Diabetes**						
	FPG^b^			≥7.0		126
	2hPG^c^			≥11.1		200
**Intermediate hyperglycemia (prediabetes)**						
	**IFG^d^**					
		FPG	6.1-6.9		110-125	
		2hPG	<7.8		140	
	**IGT^e^**					
		FPG	<7.0		126	
		2hPG	7.8-11.1		140-200	

^a^WHO: World Health Organization.

^b^FPG: fasting plasma glucose.

^c^2hPG: 2-hour plasma glucose.

^d^IFG: impaired fasting glucose.

^e^IGT: impaired glucose tolerance.

### Prevalence of Diabetes and Prediabetes in Singapore

A local study concluded that between 2010 and 2035, the prevalence of prediabetes and diabetes among Singapore residents is expected to increase by more than 2-fold, from 434,685 to 903,596 and from 373,104 to 823,802, respectively. The incidence of prediabetes and diabetes is respectively projected to increase gradually from 15.5% to 24.9% and from 13.3% to 22.7% [6]. The number of patients with diabetes in Singapore is projected to grow to 1,000,000 in 2050 [7]. It is noted that Indians have the highest prevalence of diabetes in Singapore at 17.2%, followed closely by Malays at 16.6%, and Chinese at 9.7% [8].

### Progression of the Disease

Prediabetics have a 5%-10% chance of progressing to diabetes and a higher risk of developing complications such as early nephropathy, small fiber neuropathy, early retinopathy, and risk of macrovascular disease [3,9,10].

Adults with diabetes have double the chance of contracting heart disease and stroke [11,12]. Patients with diabetes are also prone to developing kidney failure and blindness from diabetic retinopathy [13,14]. Hyperglycemia could cause neuropathy, foot ulcers, and limb amputation [15,16]. In 2021, the proportion of diabetes-related deaths in Singapore under the age of 60 years was 31.4% [17]. In addition, the total diabetes-related health expenditure worldwide in 2021 amounts to US $966 billion [17]. In Singapore, 11% of the total health care budget is set aside for diabetes [18]. It is to be noted that diabetes tends to hinder employment and productivity, putting more stress on the economy [19,20].

### Different Diagnostic Approaches From Western and Chinese Medicines

The diagnosis of diabetes and prediabetes in Western and Chinese medicines differs in the approach, methodology, and fundamental principle. Objective laboratory analysis of biochemical parameters such as fasting plasma glucose (FPG), HbA_1c_, and oral glucose tolerance tests play a crucial role in the diagnosis of diabetes in Western medicine [21]. In addition, salivary biochemical analysis is also used as a diagnostic tool for diabetes [22,23]. Diabetes and prediabetes result from inadequate insulin secretion or insulin resistance.

In contrast to Western medicine diagnostic criteria, traditional Chinese medicine (TCM) uses a different approach in the diagnosis of diabetes and prediabetes. TCM uses a unique diagnostic system to determine the underlying causes of the symptoms and devise individualized treatment plans to restore balance and promote health. Conventionally, TCM practitioners examine the patient’s body appearance, tongue and radial pulse characteristics, medical history, and symptoms to provide a comprehensive and holistic analysis of the disease syndrome. The syndrome differentiation is an assemblage of clinical manifestations resulting from the disharmony or imbalances of the body’s yin and yang, qi, and blood [24].

The ancient Chinese name of diabetes in the TCM classic “*Huang Di Nei Jing*” is known as “*xiao-ke*” [25,26]. Table 2 summarizes the syndrome differentiation of “*xiao-ke*” in the current *TCM Internal Medicine Textbook* [27].

**Table 2 table2:** Classification of “xiao-ke (消渴)” based on syndrome-etiology differentiation.

Type of syndrome and classification			Main clinical manifestations		Other symptoms
* **shang-xiao** * **上消**					
	Excess lung heat and fluid deficiency 肺热津伤	Polydipsia		Dry mouth and tongue, frequent polyuria, excessive sweating with dysphoria. The tongue tip is red with a thin yellow coating. Surging and rapid pulse.	
* **zhong-xiao** * **中消**					
	Excess stomach heat 胃热炽盛	Polyphagia, weight loss		Thirst, excessive urine, dry stool. Yellow tongue coating. Slippery and forceful pulse.	
	Qi and yin deficiency 气阴亏虚	Polydipsia		Diarrhea, with normal appetite or poor appetite, lassitude, weak limbs, and weight loss.	
* **xia-xiao** * **下消**					
	Kidney yin deficiency 肾阴亏虚	Polyuria		Excessive, turbid, sweet urine, weak and sore back and knees, fatigue, dizziness, tinnitus, dry mouth and tongue, dry skin, skin itch. Red tongue with faint coating. Fine and rapid pulse.	
	Yin and yang deficiency 阴阳两虚	Polyuria		Frequent turbid urination may even pass urine upon water intake, haggard complexion, dry ears, weak and sore back and knees, cold limbs, aversion to cold, impotence, or irregular menstruation. Pale, white, and dry tongue. Sunken, fine, and weak pulse.	

TCM provides individualized treatment plans based on the syndrome differentiation and body constitution to address the root causes of illness and promote overall well-being.

Comparing the Western medicine and TCM diagnostic approaches in diabetes and prediabetes highlights their complementary strengths. Western medicine excels in precise diagnosis and blood sugar management, while TCM offers a holistic perspective focusing on underlying imbalances. Integrating these approaches could offer a more comprehensive approach to managing diabetes and prediabetes.

### Current Possible Gaps in Syndrome Classification of Diseases

It should be noted that the syndrome classification was developed using China’s demographic data. We speculatively believe that this could be notably dissimilar from countries with tropical climates like Singapore due to the region’s specific geographical and meteorological characteristics. Local research on the body constitution of a multiracial population revealed that qi-deficiency, phlegm dampness, and damp heat were the 3 most prevalent conditions [28]. Another local study reported a significant difference in the syndrome differentiation of knee osteoarthritis, wherein a much higher proportion (51%) of these patients experience spleen and kidney deficiencies with dampness syndrome compared to only 4.2% of those in China [29].

### Conventional TCM Diagnostic Techniques

Moreover, the conventional techniques of diagnosis which rely solely on the clinical judgment, finger sensitivity, and visual accuracy of the TCM practitioner can result in inconsistent diagnoses and treatment [30,31]. For instance, the practitioner uses the index, middle, and ring fingers to simultaneously or separately palpate the bilateral radial pulses at *cun* (distal), *guan* (middle), and *chi* (proximal) locations corresponding to each viscus on each wrist (Figure 1) [31].

**Figure 1 figure1:**
[figure not shown]
(A) Location of cun, guan, and chi pulses on the radial artery. (B) Modern pulse sphygmograph and its application output in graphical and quantitative measures. (C) Application output indicating (a) palpating pressure; (b) pulse wave; (c) pulse rate per 6 seconds; (d) intensity and density of the wave spectral energy; and (e) quantitative measures of spectral energy, energy proportion, and spectral energy ratio.

Historical TCM references list 28 common pulse profiles seen in clinical practice [32]. Each radial pulse profile, with its distinct characteristics in the pulse depth, rate, waveform, density, and intensity, can reveal physiological or pathological changes in the human body [33]. For instance, Jeon et al [34] investigated pulse wave variation during the female menstrual cycle and reported that string-like or slippery and rapid pulses were seen. Subjective evaluations have been demonstrated to influence the diagnosis and treatments [31].

Aside from pulse diagnosis, tongue diagnosis is essential in distinguishing TCM syndromes. The practitioner examines the physiological and pathological changes in the tongue and associates them with specific viscera. Figure 2 provides the relationship between the tongue position and the viscera (*zang-fu*) systems. However, because observations are based on the physician’s judgment and can be easily influenced by environmental factors such as lighting and colored food, they can be highly subjective and inaccurate [35].

**Figure 2 figure2:**
[figure not shown]
Relationship of the tongue and the respective viscera in TCM concept and tongue imaging analysis. TCM: traditional Chinese medicine.

### Specific Aims and Hypothesis

This study aims to identify the gap in syndrome differentiation between the subjective and objective TCM diagnosis. We devised a protocol for a nonrandomized, exploratory, observational case-control study with equal allocations in 5 arms to investigate the syndrome differentiation of diabetes and prediabetes. We hypothesize that the local TCM syndrome differentiation of diabetes and prediabetes in the tropical climate may differ from that defined based on the Chinese demographic. We also speculate that the high-frequency spectral energy (SE_13-50Hz_) may reflect a difference in pulse wave intensity and density between the healthy and diabetes groups. We will validate the syndrome differentiation using contemporary technologies such as the tongue imaging device and the pulse sphygmograph. An objective diagnosis of the tongue could be achieved with the advancement of artificial intelligence and imaging technology [36,37]. Images of the tongue captured with the tongue diagnostic device will then be processed through an algorithm for comparison and analysis against standard tongue diagnosis images (Figure 2). Furthermore, the development of pulse sphygmographs has enabled the digitalization of pulse assessment. Researchers investigated quantitative analyses of pulse profiles in the time and frequency domains [30]. The development of these quantitative and graphical representations of the pulse profiles in the 6-pulse positions is a significant step toward transforming traditional pulse diagnoses into scientific and objective assessments (Figure 1) [31].

The objective assessment will potentially increase the accuracy of the identification, diagnosis, and prevention of diabetes and prediabetes through a targeted treatment system tailored to the local population.

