#### Pulse Sphygmograph

The Asia Plus Pen Pulse Analysis System Model PPAS-93 (Asia Plus Biotech Co, Ltd) will be used to identify pulse profiles.

The PPAS-93 is a noninvasive device that comprises a high-precision pressure sensor pen and a pulse analyzer. The high-precision pressure sensor pen is a portable handheld pen that digitalizes the biological signal of the radial pressure pulse wave and provides graphical analysis using fast Fourier transformation. This electronic gadget incorporates a high-precision pressure sensor, a filter, an amplifier, and a signal recording card connected to signal analysis software. The sampling rate is 3000 Hz, and the frequency response is between 0.1 and 50 Hz.

With the participant sitting in a relaxed position, the *cun, guan,* and *chi* pulses of each hand will be assessed using the sensor pen with appropriate vertical pressure. The result will be recorded when the best spectrogram displays the highest amplitude. A summation of SE in the 0-10 Hz (SE_0-10Hz_), 10-50 Hz (SE_10-50Hz_), and 13-50 Hz (SE_13-50Hz_) frequency ranges will be obtained. Figure 1 depicts the pulse sphygmograph and its application output.

The time domain analysis examines the amplitude and shape of the arterial waveform such as surging, slippery, fine, and thready [30]. The pulse rate per minute can be determined by the number of waves in 6 seconds multiplied by 10. This will determine the rate such as a rapid or slow pulse. The frequency domain analyzes the variation of SE in the radial pulse waves [30]. The quantitative measures can assess the intensity and density of the SE, providing insight into the deficiency, repletion, coldness, heat, or dampness syndrome. An in-depth examination of both the time and frequency domains will be conducted to deduce the associated syndrome-etiology differentiation of *xiao-ke* (Table 2).

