#### Syndrome Differentiation

The syndrome differentiation of *xiao-ke* will be based on the objective assessment results analyzed from CCMQ, tongue, and pulse diagnosis regardless of the participants’ group status. Data collection under standardized conditions using contemporary diagnostic devices is expected to enhance stability and reliability in syndrome differentiation. This approach effectively minimizes bias and eliminates the necessity for blinding in our study design.

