### Statistical Analyses

The baseline variables (age, sex, height, body weight, BMI, and blood sugar levels), MET-minutes for physical activity, scoring of body constitution, pulse assessments, and tongue analysis results will be compared between the five groups.

Using ANOVA, we will compare the variances across the means of the SE_13-50 Hz_ value from the pulse sphygmograph between each group and the control. Analysis of covariance will also be used to assess the group differences while controlling for potential confounding variables such as gender, age, BMI, physical activity levels, and others. Using the Bonferroni test for post hoc multiple comparisons, the mean values will be compared and corrected. Chi-square tests will also be used to do the comparative analysis of the body constitutions or syndromes between the objective and subjective assessments. All tests will be 2-tailed and *P*<.05 will be considered statistically significant. We will use STATA (standard edition version 18.0; StataCorp LLC) for the analysis.

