### Conclusions

To the best of our knowledge, this is the first study to use contemporary TCM diagnostic instruments to map expert and empirical knowledge of TCM to its scientific equivalents for the purpose of evaluating the syndrome differentiation of diabetes. In addition to identifying the pulse wave and tongue morphology, both devices are also capable of distinguishing the TCM body constitution and syndrome differentiation through the processing of the identified characteristics by their artificial intelligence algorithm. We will compare and contrast the outcomes of the digital analysis and the CCMQ.

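### The aim and one planned chi-square comparison set subjective against objective diagnosis, but the article describes no subjective syndrome diagnosis, and the CCMQ, the only non-device classification, is itself labelled objective

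*Protocol article*

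**What the plan says.** Specific Aims and Hypothesis gives the aim: "This study aims to identify the gap in syndrome differentiation between the subjective and objective TCM diagnosis". The matching analysis is in Statistical Analyses: "Chi-square tests will also be used to do the comparative analysis of the body constitutions or syndromes between the objective and subjective assessments".

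The Introduction explains what the subjective side is. It speaks of "conventional techniques of diagnosis which rely solely on the clinical judgment, finger sensitivity, and visual accuracy of the TCM practitioner", and the Discussion (Expected Findings) returns to finger sensitivity and visual assessment of the tongue as the source of subjectivity.

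For the study's own data, the Pulse Sphygmograph section says: "The Asia Plus Pen Pulse Analysis System Model PPAS-93 (Asia Plus Biotech Co, Ltd) will be used to identify pulse profiles". The Tongue Diagnosis section assigns the tongue reading to an artificial-intelligence imaging system and adds that its results will be reconciled with the pulse diagnosis and the CCMQ. According to the Syndrome Differentiation section, the xiao-ke syndrome "will be based on the objective assessment results analyzed from CCMQ, tongue, and pulse diagnosis". The Conclusions of the Discussion state: "We will compare and contrast the outcomes of the digital analysis and the CCMQ".

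**The concern.** A comparison of two diagnostic routes needs a classification from each route, on the same scale, for the same participants. The aim concerns syndrome differentiation. For the subjective route, the article describes no step at which anyone records a syndrome by conventional means.

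What is at stake is the meaning of the result. Disagreement between a device and a constitution questionnaire could be reported as a gap in conventional TCM diagnosis, or as evidence of practitioner inconsistency. It would be neither, because no practitioner's reading enters the comparison. The CCMQ's double role adds a second problem. If it is both the comparator and an input to the result it is compared with, the two sides are not independent.

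**Working it through.** No arithmetic decides this point, and the plan gives no figure to reproduce. The check sets what the comparison needs beside what the article says is collected.

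**1. What is needed.** The aim needs a subjective and an objective syndrome for each participant. The planned chi-square comparison needs a subjective and an objective body constitution, or syndrome, for each participant.

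**2. What is collected.** Table 3 has four assessment rows:

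| Row in Table 3 | How the procedures describe it | Practitioner diagnosis? |
|---|---|---|
| Health evaluation | Vital signs, blood sugar, BMI, medications, symptoms | No syndrome assigned |
| Questionnaires | Physical activity, sugar intake, CCMQ | No |
| Pulse diagnosis | Sensor pen and analyser; it "will be used to identify pulse profiles" | No palpation reading described |
| Tongue diagnosis imaging | Camera and artificial-intelligence system | No visual reading described |

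Practitioner diagnoses described as study data: 0 of 4 rows. A TCM physician's syndrome diagnosis appears once, under Recruitment of Participants (spleen and stomach deficiency), and there it is an exclusion criterion.

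**3. Can the CCMQ serve as the subjective side?** The Conclusions of the Discussion suggest that this may be the intention. Taking the two halves of the planned comparison in turn:

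- *Syndromes.* The CCMQ section describes 60 questions scored into 9 body constitutions. Table 2 lists 1 + 2 + 2 = 5 xiao-ke syndromes under its three headings. The article gives no rule that turns a CCMQ constitution into one of these syndromes. The syndrome half therefore has data on the objective side only.
- *Body constitutions.* The Tongue Diagnosis section says the system's body constitution will be recorded, and the Conclusions say both devices can distinguish it. A device-versus-CCMQ comparison can therefore be made. Its non-device side is a scored Likert questionnaire, which the exclusion criteria indicate the participant must be able to complete. Finger sensitivity and visual judgement play no part in it.

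**4. Is the CCMQ kept apart from the objective side?** No, in two places:

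- The Syndrome Differentiation section names it among the objective results from which the syndrome is derived. Comparing that syndrome with the CCMQ would set a composite against one of its own components.
- The Tongue Diagnosis section reconciles the tongue results with the pulse diagnosis and the CCMQ. The article does not say what reconciling involves. If device results are adjusted in that step, some of the disagreement to be measured is removed beforehand.

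**5. What does not depend on this.** The two stated hypotheses (local syndrome pattern versus that defined on the Chinese demographic, and SE 13-50 Hz in healthy versus diabetes groups) use no subjective comparator. Neither do the ANOVA, the analysis of covariance or the sample-size rationale.

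**The case against.** Four arguments can be made for the plan.

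- **The article is condensed.** Protocol version 1.8 and the flow figure are not shown, and either could contain a practitioner reading. The Study Procedure section also speaks of training to reduce variability between physicians, so physicians take some part. This stands as a limit on certainty. A reader might infer that practitioner diagnoses are definitely not collected, and the document does not support that inference. What it does show is that the aim and analysis do not match the article's own itemised schedule and explicit syndrome rule. The objective label on the CCMQ is on the page whatever the full protocol says.
- **A comparison with the CCMQ is available.** This stands for body constitution. A reader might infer that the whole objective-versus-subjective comparison cannot be run, but that goes too far. Only the syndrome half lacks a subjective side.
- **Symptoms are recorded.** Health Evaluation collects existing symptoms to relate them to syndrome differentiation, and Table 2 defines the syndromes largely by symptoms. It would be wrong to say that nothing subjective bearing on syndromes is collected. Still, a list of symptoms is not a syndrome diagnosis, and no rule is given for turning it into one.
- **The Abstract words its aim differently.** It speaks of a gap in conventional techniques, studied with contemporary devices. A reader might take this as a head-to-head comparison with practitioners, but the Abstract does not say so. The explicit contrast appears in the aim sentence of the main text and in the chi-square sentence.

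**Conclusion.** The point holds in a limited form. As described in the article, the syndrome comparison has no subjective side. The constitution comparison is feasible but sets devices against a self-report questionnaire. The CCMQ appears both as the likely comparator and as an objective input.

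The defect affects one aim sentence, one chi-square comparison and the conclusions drawn from them. A reader might infer that the study as a whole cannot deliver. The document does not support this: the design is described as exploratory and as a pilot, and both stated hypotheses and the SE 13-50 Hz analysis stand apart from this comparison.

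The conclusion assumes that Table 3 and the procedure sections are a complete list of the assessments. It should be fixed. Confidence is moderate because the full protocol is not shown.

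**What to change.** 1. In Specific Aims and Hypothesis and in Statistical Analyses, restate the comparison as agreement between device-derived and CCMQ-derived body constitution, and remove syndromes from it. Both classifications come from the same participants, so a paired agreement measure such as kappa fits this wording. A chi-square test of independence addresses association, not agreement.
2. In Syndrome Differentiation, stop labelling the CCMQ as objective. State that the comparison uses device output as it stands before the reconciliation described under Tongue Diagnosis.
3. Do not claim from this comparison a gap in conventional practitioner diagnosis, in the Abstract or in the main text.
4. If the full protocol does collect a practitioner diagnosis, reconcile Table 3 and the syndrome rule with it instead of making changes 1 to 3.

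The cost is wording only, with a narrower claim; no new data are needed. Rewording is also the practical route. By July 15, 2024, 140 of 250 participants had been enrolled, so a practitioner reading added from that date could cover at most 250 − 140 = 110 new participants (110/250 = 44%).

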#### Tongue Diagnosis

The China Artificial Intelligence Health Status Identification System Model YZKJ-SMZY-1AI will be used to image and analyze the participant’s tongue. The noninvasive device captures the image of the tongue through an inbuilt camera supported by light-emitting diode lighting within the device within 15 seconds. A monitor connected to the imaging instrument would display real-time video feedback on the tongue’s position. Using an artificial intelligence system, the photographs of the face, tongue, and sublingual collaterals will be examined and compared with typical images of tongue analysis within 10 seconds. Figure 4 depicts the analytical details of the tongue, including the shape and color of the tongue, the texture and color of the tongue coating, the moisture level of the tongue, and the sublingual collaterals. The body constitution and syndrome differentiation will be analyzed and recorded. Figure 5 provides some examples of body constitutions and syndrome differentiation reported from the system. The results will be reconciled with the pulse diagnosis and CCMQ.

Before evaluation, the participants will be instructed to abstain from tongue scraping, smoking, and consuming caffeinated beverages such as coffee, tea, and cola, as well as dairy products such as milk, yogurt, and cheese, which may alter the tongue diagnosis.

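### The tongue and pulse devices are said to validate the syndrome differentiation, but they are inputs to the syndrome label, and the article defines no label made without them

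*Protocol article*

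**What the plan says.** Specific Aims and Hypothesis (Introduction) gives the devices a validating role: "We will validate the syndrome differentiation using contemporary technologies such as the tongue imaging device and the pulse sphygmograph".

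The Methods then describe how the syndrome is reached:

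- Syndrome Differentiation: the xiao-ke syndrome "will be based on the objective assessment results analyzed from CCMQ, tongue, and pulse diagnosis".
- Pulse Sphygmograph: "An in-depth examination of both the time and frequency domains will be conducted to deduce the associated syndrome-etiology differentiation", with reference to Table 2.
- Tongue Diagnosis: "The body constitution and syndrome differentiation will be analyzed and recorded", and then "The results will be reconciled with the pulse diagnosis and CCMQ".

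The Conclusions add that "both devices are also capable of distinguishing the TCM body constitution and syndrome differentiation".

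Three comparisons are planned that bear on the matter. Statistical Analyses has a chi-square comparison of objective with subjective assessments of constitution or syndrome. The Conclusions plan to set the digital output against the CCMQ. Expected Findings plans an exploratory correlation of the syndrome with the WHO criteria for diabetes.

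**The concern.** If an instrument helps to make a label, its agreement with that label is partly built in. This is incorporation bias: the test under study is part of its own reference. Such agreement does not show that the device output is correct.

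The article rests a good deal on the devices being right. The Abstract expects dependable and unbiased results from them. Expected Findings speaks of establishing the reliability of the tools as a step towards wider clinical use. Syndrome Differentiation relies on standardised device data to argue that blinding is not needed. A validation claim that rests on agreement with a composite containing the devices would support none of these.

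**Working it through.** The article states no agreement figure, kappa or sensitivity for the validation, so there is nothing to reproduce. The check is mainly a reading of the text, with one illustration of size.

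**1. What goes into the label.** Syndrome Differentiation lists three inputs: CCMQ, tongue and pulse. The Pulse Sphygmograph and Tongue Diagnosis sections confirm that each device output feeds the syndrome and that the sources are reconciled with one another. So 2 of 3 inputs are the validating instruments. The third is a questionnaire.

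**2. Is there a label without device input?**

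- The study schedule (Table 3) lists health evaluation, questionnaires, pulse diagnosis and tongue imaging. It shows no separate practitioner syndrome diagnosis.
- Statistical Analyses names a subjective assessment but does not say what it is.
- The CCMQ is the only visible candidate. Syndrome Differentiation counts it as objective, and it is inside the composite. It also scores nine body constitutions, whereas Table 2 has five xiao-ke syndromes, so it cannot by itself be the reference for the syndrome.
- The WHO criteria are external, but a correlation with them tests association with diabetes status. It does not test whether the right syndrome was assigned.

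**3. Illustration of size.** The article gives no reconciliation rule. Assume that three independent, uninformative inputs each choose among k equally likely categories, that the label is their majority, and that a three-way split goes to one input at random. For one device:

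- P(agrees with label) = P(matches at least one other input) + P(all three differ)/3
- = [1 − ((k−1)/k)²] + [(k−1)/k × (k−2)/k]/3
- Chance agreement = 1/k, and kappa = (P − 1/k)/(1 − 1/k)

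| k | Matches another | All differ, /3 | Agreement | Chance | Kappa |
|---|---|---|---|---|---|
| 2 | 0.75 | 0 | 0.75 | 0.50 | 0.50 |
| 5 | 0.36 | 0.48/3 = 0.16 | 0.52 | 0.20 | 0.32/0.80 = 0.40 |
| 9 | 0.21 | 0.69/3 = 0.23 | 0.44 | 0.11 | 0.33/0.89 = 0.37 |

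Devices carrying no information would show agreement clearly above chance, though far from complete. These figures estimate nothing in this study: the majority rule is assumed, and because the CCMQ scores constitutions it could not cast the vote on the five syndromes that the k = 5 row supposes.

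**The case against.** A reader might infer that the validation cannot fail. The documents do not support that. The objective-versus-subjective comparison, the digital-versus-CCMQ comparison and the correlation with WHO criteria can each show disagreement or no association. Even in the noise illustration, agreement with five categories is 52%, not 100%.

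A reader might also infer that the study will report device-versus-composite agreement as its validation. No such analysis is listed. Statistical Analyses has group comparisons, ANOVA and ANCOVA of the high-frequency spectral energy, and the chi-square comparison. The sentence in the aims may only mean that conventional syndrome differentiation is checked with devices, or may be loose wording for determining it.

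A third point is that a non-device comparator is named and may be defined in the full protocol, which is not shown. That is fair. The missing detail is therefore not the finding here, and it would be wrong to say that no such comparator exists. Likewise, the device reports are stored as PDFs (Data Management and Monitoring), so source-level results should survive reconciliation.

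What remains is a conflict between two statements in the article as published: the devices validate the syndrome, and the devices help to make it. A definition of the subjective assessment elsewhere could supply a proper reference, but the composite in Syndrome Differentiation would still not be one.

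An obvious remedy, a reference syndrome built from symptoms plus CCMQ, is itself open to question. Four of the five syndromes in Table 2 are described partly by tongue and pulse signs, so that label would depart from the study's own definition, and the CCMQ is already in the composite. It is not recommended here.

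**Conclusion.** The concern holds in a limited form. The article claims a validation that the design it describes does not contain, because the two validating devices are two of the three sources of the xiao-ke label and no label independent of them is defined. Agreement of a device with the composite would be biased upwards and should not be read as validation.

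The size cannot be given for this study. The kappas of 0.40 to 0.50 for five and two categories (0.37 for nine) are illustrative only and depend on a majority rule, equal categories and independent inputs, none of which the article states. The conclusion does not depend on them; it follows from the passages set side by side. It concerns what may be claimed from the study and does not affect the group comparisons of spectral energy.

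**What to change.** 1. In Specific Aims and Hypothesis, replace *validate* with *determine*, and state that agreement of a device with the composite syndrome will not be presented as validation.
2. Analyse each source's result as recorded before the reconciliation described under Tongue Diagnosis.
3. Report chance-corrected agreement (kappa with 95% CI) for body constitution between the tongue device and the CCMQ, and between the pulse device and the CCMQ where the pulse device outputs a constitution. A chi-square test alone shows association, which is not the same as agreement.
4. Claim validation of the xiao-ke syndrome only if the subjective assessment named under Statistical Analyses is a label made without device output, and say so there.

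Cost: a wording change and one agreement table from data already being collected, with no extra visit, provided the results before reconciliation have been kept for the participants already enrolled (140 at 15 July 2024). The categories of the devices and the CCMQ must be put on a common list. The price is that observed agreement will look lower than against the composite, and the validation claim becomes narrower.
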